# Efficacy, safety and therapeutic mechanism of Shen-Qi Xiao-Tan formula in the treatment of peripheral atherosclerosis in patients with type 2 diabetes mellitus: a randomized, double-blind, placebo-controlled trial protocol

**DOI:** 10.1186/s12906-022-03813-9

**Published:** 2022-12-22

**Keywords:** Type 2 diabetes mellitus, Peripheral atherosclerosis, Chinese herbal medicine, Randomized controlled trial, Shen-Qi Xiao-Tan formula

## Abstract

**Background:**

Peripheral atherosclerosis is a common macrovascular complication of diabetes, but the treatment is limited. Chinese herbal medicine is the complementary and alternative therapy to delay the progression of atherosclerosis and reduce blood glucose and lipids. Shen-Qi Xiao-Tan (SQXT) formula is one of the prescriptions commonly used to treat diabetic peripheral atherosclerosis, but there is still a lack of high-quality evidence-based evidence.

**Methods:**

This is a randomized, double-blind, placebo-controlled add-on trial that is expected to enroll 114 diabetic patients with peripheral atherosclerosis. After a 2-week run-in period, participants will been randomly assigned in a 1:1 ratio and receive 12 weeks of usual treatment and SQXT formula (treatment group) or usual treatment and placebo (control group). The primary outcome is the change in carotid intima-media thickness from baseline to endpoint. The secondary outcomes are the structure and function of peripheral arteries, blood glucose and lipids, traditional Chinese medicine syndrome score, and quality of life, and safety and endpoint events are evaluated. To explore the therapeutic mechanism through oxidative stress, inflammation, and advanced glycation end products, and lipidomics will be used to screen for biomarkers for diagnosis and efficacy evaluation.

**Discussion:**

The objective of this trial is to evaluate the efficacy, safety and therapeutic mechanism of SQXT formula in the treatment of diabetic peripheral atherosclerosis. It will obtain high-quality evidence-based evidence and promote the treatment of diabetic macroangiopathy and the research and development of new drugs.

**Trial registration:**

This trial is registered on Chinese Clinical Trials.gov with number ChiCTR2100047189 on 10 Jun 2021, and has been approved by the Ethical Review Committee of Hospital of Chengdu University of Traditional Chinese Medicine with number 2020KL-080.

## Background

Diabetes, as one of the major chronic diseases that threaten human health, has become a world-wide public health problem. According to the International Diabetes Federation Diabetes Atlas (10th edition), there are about 537 million people living with diabetes worldwide [1]. It estimates that total diabetes-related health expenditure will reach USD 1.03 trillion by 2030 [1]. Diabetes and its complications have brought heavy medical and economic burdens to individuals and society.

Macroangiopathy is the main cause of death and disability in diabetes, with atherosclerosis as the basic pathological alteration. Compared with non-diabetic patients, type 2 diabetic patients with atherosclerosis have the characteristics of earlier onset, more severe degree, and wider range of disease [2–5]. In China, the total number of diabetic patients is about 140.9 million, ranking first in the world [1]. The China DIA-LEAD study shows that the prevalence of macroangiopathy in diabetic patients is as high as 55.6% in China, and peripheral vascular disease is the most common one, with the prevalence of about 31.4% [2]. Atheroscleroses of the carotid and lower extremity arteries are one of the most common causes of peripheral artery disease. Carotid artery atherosclerosis can further cause head and neck artery stenosis, atherosclerotic stroke, transient ischemic attack, myocardial infarction, etc. [6]. Lower extremity arteries atherosclerosis can further causes lower extremity artery disease, diabetic foot ulcers, limb gangrene, amputation, and it is an important risk factor for cardiovascular events [7–9]. Globally, an adult dies from diabetes and its complications every 8 s, and a patient is lost to lower extremity amputation every 30 s as a consequence of diabetes [1, 10, 11]. Approximately 75% of diabetics die from macroangiopathy [12, 13]. A series of complications caused by peripheral atherosclerosis have caused the increase of readmission rates and length of stay, the raise of medical costs, and the consumption of a large number of medical and public health resources [14, 15]. Therefore, delaying peripheral atherosclerosis progression as soon as possible to reduce the occurrence of fatal and disabling events is the key content of diabetes management.

At present, the clinical prevention and control measures for diabetic macroangiopathy include strict blood glucose control, anti-hypertensive agents, lipid lowering therapies, anti-platelet agents, etc. But the comprehensive clinical control rate is only 8.1% [2]. A number of large clinical trials have shown that strict blood glucose control is associated with increased risk for death in diabetic patients at high risk of cardiovascular events [16–19]. The Look AHEAD Research found that intensive lifestyle intervention was associated with increased risk for primary cardiovascular outcome in patients with poor glucose control (HR 1.85, 95%CI 1.32–2.61) [20]. How to comprehensively relieve diabetic peripheral atherosclerosis is a challenging clinical issue.

In China, Chinese herbal medicine (CHM) is widely used to treat diabetic macrovascular complications. A systematic review and meta-analysis has shown that CHM can reduce blood glucose and haemoglobin A1c (HbA1c), ameliorate lipid metabolism disorders, and improve Traditional Chinese Medicine (TCM) syndrome scores in the treatment of diabetic macrovascular disease [21]. Shen-Qi series formulas have efficacy for alleviating insulin resistance, promoting b-cell function, and improving intestinal microbiota in the treatment of patients with type 2 diabetes mellitus (T2DM) [22, 23].In addition, it can reduce blood interleukin-6 (IL-6), hs-C-reactive protein and carotid intima-media thickness (CIMT), alleviate clinical symptoms, and improve quality of life in diabetic patients with macroangiopathy [24, 25]. Furthermore, the mechanism of Shen-Qi series formulas in delaying the progression of diabetic atherosclerosis has been proved from epigenetic DNA methylation, PI3K-Akt pathway, glucagon-like peptide-1 and other aspects [26–28]. A systematic review and meta-analysis has shown that the efficacy of Shen-Qi series formulas combined with usual treatment is superior to that of usual treatment in the treatment of type 2 diabetic macrovascular complications, it can reduce fasting and postprandial blood glucose, C-reactive protein and leptin, and improve adiponectin [29]. On the other hand, it has found that there are deficiency in previous clinical trials, such as lack of allocation concealment and blinding methods, and small sample size, which led to limited quality of trials.

In summary, CHM can regulate the overall pathological status of diabetic patients with macroangiopathy through multi-target, but there is a lack of high-quality clinical trials. This trial will comprehensively evaluate the efficacy, safety and therapeutic mechanism of Shen-Qi Xiao-Tan (SQXT) formula in the treatment of peripheral atherosclerosis in T2DM from the structure and function of peripheral arteries, cardiovascular events, lipid metabolism, inflammation, oxidative stress and advanced glycation end products (AGEs).

### Objective

#### Primary objective

The primary objective of this trial is to determine whether SQXT formula is superior to placebo to relieve peripheral atherosclerosis in T2DM by evaluating the following outcomes.Change in CIMT.Changes in the structure and function of peripheral arteries, including (1) hyperechoic thickness of the arterial lumen wall, vascular internal diameter, peak systolic velocity (PSV), end diastolic velocity (EDV), mean velocity (Vm), pulse index (PI) and resistance index (RI) of lower extremity and carotid arteries; (2) flow-mediated vasodilation (FMD); (3) ankle brachial index (ABI).Levels of glucose and lipid profile indices.TCM syndrome score.Quality of life as measured by multiple questionnaires.

#### Secondary objectives

This trial also aims to evaluate safety and explore therapeutic mechanism of SQXT formula in treating patients with diabetic peripheral atherosclerosis.

## Methods/design

### Study design

This trial is registered on Chinese Clinical Trials.gov with number ChiCTR2100047189 on 10 Jun 2021. It is a randomized, double-blind, placebo-controlled, add-on trial. 114 subjects are expected to be enrolled. After a 2-week’s run-in period, participants who meet the standards of the run-in period are randomly assigned to 12 weeks of either placebo group or treatment group on a 1:1 allocation. The flow chart of the trial is shown in Fig. 1. This protocol follows the requirements of the *Standard Protocol Items for Randomized Trials* (SPIRIT) and the *Consolidated Standards of Reporting Trials* (CONSORT) Extension for CHM Formula [30, 31].

**Fig. 1 Fig1:**
[figure not shown]
The flow chart of the trial

### Inclusion criteria

According to *Standards of Medical Care in Diabetes*, *Guideline for the Prevention and Treatment of T2DM in China*, and *Guideline for Ultrasound Examination of Blood Vessels and Superficial Organs*, [32–34]patients with definite diagnosis of T2DM;color doppler ultrasound of the carotid or lower extremity arteries showed intima-media thickening (IMT ≥ 1 mm) and/or atherosclerotic plaque (limited IMT ≥ 1.5 mm).Patients with the following symptoms of TCM syndromes: thirst, fatigue, body fat, dietary predilection of fat and sweets, etc. According to *Guiding Principles for New Drug Clinical Research of TCM* and *Guidelines for Prevention and Treatment of Diabetes in TCM*, the diagnostic criteria of deficiency of both qi and yin with phlegm-turbidity syndrome are defined on the standards and expert advice [35, 36].Aged between 30 and 65 years old.Patients participate voluntarily and sign the Informed Consent Form (ICF).Women of childbearing age must have a negative urine pregnancy test and agree to use reliable contraception during this trial.

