#### Outcome measurement

Changes of the following outcomes from baseline (week 0) to endpoint (week 12) of intervention will be evaluated.

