### Sample size

This is a randomized, double-blind, placebo-controlled superiority trial. The primary outcome indicator, CIMT, is used as the basis for sample size estimation. The mean of CIMT of the placebo group is 1.12 mm [40–42]. In this trial, the mean of CIMT of the treatment group is estimated at 1.03 mm, and the standard deviation of two groups is 0.10. The superiority margin is 0.03 (one-sided test, α = 0.025, 1-β = 0.8). The sample allocation ratio between the two groups is 1:1. Using PASS 15 software, the minimum sample size is calculated to be 90. In addition, considering the dropout rate of 20%, we plan to enroll a total of 114 participants.

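### Patients may enter on leg-artery disease alone, but the primary outcome and the sample size rest on carotid IMT, so power may be lost to an unknown extent

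*Protocol article*

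**What the plan says.** **Entry.** Inclusion criteria, protocol article: "color doppler ultrasound of the carotid or lower extremity arteries showed intima-media thickening (IMT ≥ 1 mm) and/or atherosclerotic plaque (limited IMT ≥ 1.5 mm". The two arterial territories are joined by an or, and so are thickening and plaque. Exclusion criteria sets no minimum carotid IMT. The targets that must be met before randomisation (Run-in period) concern glucose, blood pressure and LDL-C only.

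**Outcome.** Abstract, Methods: "The primary outcome is the change in carotid intima-media thickness from baseline to endpoint". Primary efficacy outcome lists CIMT and nothing else, and Outcome measurement places the change "from baseline (week 0) to endpoint (week 12) of intervention". Leg-artery measures appear under Secondary efficacy outcomes.

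**Sample size.** "The primary outcome indicator, CIMT, is used as the basis for sample size estimation". The inputs are "The mean of CIMT of the placebo group is 1.12 mm", referenced to three outside sources, and "the mean of CIMT of the treatment group is estimated at 1.03 mm". The SD is 0.10, the superiority margin 0.03, one-sided alpha 0.025 and power 0.80. The result is 90 evaluable and 114 enrolled after 20% dropout.

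**Analysis.** Data analysis names ordinary between-group tests at p ≤ 0.05 without mentioning the margin. The only subgroup it names is by HbA1c.

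**The concern.** The artery that qualifies a patient need not be the artery in which efficacy is measured. Someone with femoral thickening and an unremarkable carotid wall meets the ultrasound criterion as written, yet may have little carotid thickening for treatment to reduce. The planning values, by contrast, look like a population thickened in the carotids. If CIMT on placebo were Normal with mean 1.12 and SD 0.10 mm, about 88% of participants would be at or above 1.0 mm (z = (1.00 − 1.12)/0.10 = −1.2). The entry rule does not secure such a population.

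Two things are at stake. One is power: entrants with a smaller achievable change pull the difference between arms towards zero, and the sample size has no reserve against its margin. The other is interpretation: after a null CIMT result, one would have to ask whether the product failed or whether too many participants had little to improve at the measured site.

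**Working it through.** **1. Reproduce the plan's figure.** Inputs from Sample size: means 1.12 and 1.03, SD 0.10 (unit not stated, taken as mm), margin 0.03, one-sided alpha 0.025, power 0.80, allocation 1:1.

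- Effective difference: (1.12 − 1.03) − 0.03 = 0.06 mm.
- Normal approximation: n = 2 × (1.96 + 0.842)² × 0.10² / 0.06² = 43.6, so 44 per arm.
- Noncentral t: 45 per arm, 90 in total, power 0.804.
- Dropout: 45 / 0.8 = 56.25, so 57 per arm and 114 in total.

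Both stated figures are reproduced. There is no arithmetic error.

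**2. Dilution.** Let p be the share of leg-only entrants. The document does not give it, so 10, 20 and 30% are assumed. Let their CIMT effect be zero, which is the worst case. Then

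- d = 0.09 × (1 − p)
- SE = 0.10 × √(2/45) = 0.0211
- power against the margin = Φ((d − 0.03)/SE − 1.96)
- power against zero = Φ(d/SE − 1.96)

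| p | d (mm) | d − 0.03 (mm) | Power, 0.03 margin | Power, zero difference |
|---|---|---|---|---|
| 0% | 0.090 | 0.060 | 81% | 99% |
| 10% | 0.081 | 0.051 | 68% | 97% |
| 20% | 0.072 | 0.042 | 51% | 93% |
| 30% | 0.063 | 0.033 | 35% | 85% |

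Noncentral t gives 67, 50 and 34% against the margin for the last three rows. On the same basis, 80% power would need 124, 180 and 292 evaluable participants (156, 226 and 366 enrolled).

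The margin steepens the loss: a 20% cut in the 0.09 mm effect is a 30% cut in the effective difference (0.060 to 0.042).

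**3. Milder assumption.** If 20% are leg-only entrants who get half the effect, d = 0.8 × 0.09 + 0.2 × 0.045 = 0.081 mm. Power is about 68% against the margin.

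**4. Spread.** Suppose leg-only entrants average 0.85 to 0.95 mm (assumption) and p = 20%. The SD of CIMT values is then √(0.10² + 0.2 × 0.8 × (1.12 − m)²), which is 0.147 at m = 0.85 and 0.121 at m = 0.95. This applies only if endpoint values are compared. With change from baseline, a lower starting level largely cancels, and mainly the dilution of the mean in step 2 remains.

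**The case against.** The broad entry rule fits the stated target. The objective concerns peripheral atherosclerosis, leg-artery measures are secondary outcomes, and the Discussion defends CIMT as an early marker of peripheral atherosclerosis. The share of leg-only entrants may be near zero. The Discussion also treats CIMT risk as graded per 0.1 mm, so a response need not vanish below 1 mm. Baseline CIMT is recorded for everyone, so a null result can be examined by baseline level. The analysis plan, which is not shown, may already adjust for baseline.

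Much of this stands, and it limits the point. A reader might infer three stronger things that the document does not support:

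- **That leg-only entrants invalidate the 1.12 mm premise.** The populations behind that figure are not shown, so it may already reflect a mix. Moreover, only the 0.09 mm difference, the SD and the margin drive the sample size; the level of 1.12 mm does not.
- **That such entrants cannot respond.** Zero response is an assumption at the severe end.
- **That the trial is certainly underpowered.** The share is unknown, and the steep loss belongs to the margin test in Sample size. Data analysis mentions no margin, and against a zero difference power stays at 85% or more over the assumed range.

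What the objection does not remove is the mismatch itself. If broad entry is intended, the 0.09 mm effect needs to be justified for that mixed population, and Sample size gives no such justification. An analysis plan can help to interpret the result, but it cannot undo dilution that enrolment has produced.

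**Conclusion.** The point holds as a mismatch, of unknown size, between the entry rule on one side and the primary outcome and its sample size on the other. It is a matter of power and interpretation. With 45 per arm, SD 0.10 mm and zero effect in an assumed 10 to 30% of participants, power falls to between 68 and 35% against the 0.03 mm margin, or to between 97 and 85% against a zero difference. Which of these applies depends on whether the margin is actually tested. The mismatch can be read directly from the text; the size of the loss cannot. It merits a correction, and most of that can be made with data the trial already collects.

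**What to change.** Before unblinding, and in the analysis plan if it is not already there:

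1. Specify the primary CIMT comparison as adjusted for baseline CIMT. This deals with differences in starting level; it does not restore a diluted mean effect.
2. Add a pre-specified analysis in participants with carotid disease at baseline, defined as carotid IMT ≥ 1 mm or carotid plaque, and report it beside the full-set result. Naming plaque keeps those who qualified on carotid plaque with a lower measured CIMT.
3. Word the CIMT conclusion for the carotid arteries, not for peripheral atherosclerosis as a whole.
4. State that the 80% power assumes carotid disease in essentially all participants, or restate it for the mixed population with the assumed share and response given.

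The cost is one extra analysis, less precise because it uses a subset, and a sentence or two of text. No new measurement is needed.

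Restricting the remaining enrolment to patients with carotid disease is an option for the sponsor to weigh, since Trial status describes recruitment as ongoing. It would slow recruitment, narrow the population and leave the trial with two entry populations.

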### Exclusion criteria

Patients with calcified plaques or unstable plaques in lower extremity or carotid arteries, arterial stenosis (vascular inner diameter stenosis ≥ 50%), or arterial occlusion.Patients who have been diagnosed with coronary heart disease by coronary angiography, or whose electrocardiogram and clinical manifestations suggest coronary heart disease, or who have had cardiovascular and cerebrovascular events, such as acute coronary syndrome and cerebral infarction.ABI ≤ 0.9.Fasting TG > 5.7 mmol/L.Patients with abnormal liver and kidney function, such as the ratio of serum alanine aminotransferase (ALT) to aspartate aminotransferase (AST) 1.5 times higher than the upper limit of normal value of that, creatinine higher than the upper limit of normal value of that, estimated GFR ≤ 60 ml·min^−1^·(1.73m^2^)^−1^.Patients with acute metabolic disorders such as diabetic ketoacidosis, or severe stress, occurred within 1 month before screening.Patients with serious illnesses whose life expectancy does not exceed 2 years, or malignant tumor, or mental diseases.Patients who are known to be allergic to the ingredients in SQXT formula or its preparations.Having a history of alcoholism or drug abuse.Women who are preparing for pregnancy, or pregnant, or lactating women.

### Recruitment

Participants will be recruited from Hospital of Chengdu University of TCM. This is also China National Clinical Research Base of TCM for diabetes.

### Randomization

The random sequence was generated by the third-party statistician from the Sichuan Province Evidence-based Medicine Center of TCM using R software (version 4.0.3), including 114 random numbers in a 1:1 ratio between the treatment group and the control group. It was concealed by opaque sealed envelopes.

### Blinding

Investigators, participants, outcome assessors, and data analysts will be blinded. Outcome assessors will follow the standard operating procedure to complete tests. The third-party drug management staff from the Sichuan Province Evidence-based Medicine Center of TCM will blind investigational drugs according to random sequence, so that the drugs could not be distinguished according to their numbers. The drug management staff shall not directly participate.

The data analysts will be unblinded at the first level after the database is locked, and unblinded at the second level after statistical analysis is completed. In case of emergency such as serious adverse event and suspected unexpected serious adverse reaction, the participant’s allocated intervention will be revealed urgently, and investigator should treat he and record the time, date and reason of unblinding.

In order to ensure stability of the drugs, increase convenience of taking medicine, and remove the influence factors such as the method of decoction and the origin of medicinal materials, SQXT formula and placebo will be used in granules form. In accordance with the *Standard for the Use of Food Additives in the National Standard for Food Safety*, the placebo is made from maltodextrin and food additives such as food colorants and bitters. SQXT formula and placebo are similar in color, smell, taste, appearance, packaging, and tag. Both of them are produced by Sichuan Neo-Green Pharmaceutical Technology Development Co. Ltd. (Sichuan, China).

### Interventions

#### Run-in period

In order to standardize the usual treatment, obtain the baseline values of blood glucose, blood lipid and blood pressure (BP), and ensure the compliance of participants, participants will enter a 2-week’s run-in period after passing the screening.

According to the recommendations of multidisciplinary guidelines, the investigators will decide the usual treatment based on the participants' personal situation [32, 33]. All participants will receive the same lifestyle behavior management education in diabetes self-management, diet, and routine physical activity. All of them will be treated with standard treatment of glucose-lowering medications and antihypertensive medications, as well as atorvastatin to lower lipid.

Participants should not use other CHM, acupuncture, Tuina and other TCM interventions outside of this trial, as well as drugs with potential risk of cardiovascular disease events. In consideration of clinical practice and ethical principles, drugs with demonstrated cardiovascular disease benefits will not prohibited in this trial.

Participants will be assigned randomly to the intervention period only if their blood glucose, blood lipid and BP reach the following targets [32, 33, 37, 38]: (1) fasting plasma glucose (FPG) between 4.4 and 7.0 mmol/L; (2) non-fasting blood glucose < 10.0 mmol/L; (3) BP ≤ 140 / 90 mmHg; and (4) low-density lipoprotein cholesterol (LDL-C) < 3.4 mmol/L.

